### Data Management

Data will be collected on case report forms and source documents pertaining to the questionnaires mentioned earlier in this paper and stored at the Providence Care Hospital. It will then be entered into a secure web-based database at the Providence Care Hospital and will only be accessible by the study team. To ensure confidentiality during the study, subject data will be analyzed under a randomized assigned study number. Participants’ study files will be kept in a designated locked room, only accessible by the study co-coordinator and study investigators for 25 years, as per the International Council for Harmonisation of Technical Requirements for Pharmaceuticals for Human Use (ICH) guidelines.

Blood and fecal samples will be stored at the Providence Care Hospital until the time of transfer, which will occur intermittently throughout the study. A material transfer agreement will be in place as per the Health Sciences and Affiliated Teaching Hospitals research ethics board (HSREB) protocol for all biological specimen transfers.

### Statistical Analyses

Treatment success and failure will be measured individually. Those who have an improvement of at least 50% in MADRS or GAD-7 scores will be considered responders. The SPSS will be used to analyze all data from clinical measures obtained throughout the study. Repeated measures analysis of variance (ANOVA) will be used to analyze changes in clinical measures from baseline to week 10. Paired *t* tests will be used to compare clinical measure means at each time point with the baseline. If a participant returns after the first course of treatment and is later withdrawn, their final scores for primary outcomes will be projected to week 10. In the event of missing data, the data from the last time point will be projected forward. Similarly, stool samples will be analyzed to provide diversity scores, which will then be compared using paired *t* tests and repeated measures ANOVA. Changes in diversity scores will be compared with clinical scores to assess for correlations.

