### Objectives

#### Primary Objective

The primary objective of this study is to assess subjective changes in mood and anxiety symptoms before, during, and after MET-2 treatment in participants with major depression and/or generalized anxiety, using the Montgomery-Asberg depression rating scale (MADRS), GAD 7-item scale (GAD-7), and other mood/anxiety scales. Those with a 50% reduction in the GAD-7 and/or MADRS scores will be considered successful responders to treatment.

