## Methods

### Study Design

This is an 8-week, open-label, phase 1 clinical trial assessing the safety, tolerability, and efficacy of MET-2 on depression and anxiety symptoms. All participants will consume the investigational product, MET-2, in *a* capsule form, daily for 8 weeks. MET-2 is administered orally at 0.5 g of MET-2 per capsule, containing 3.2 ×10^5^-3.2×10^11^ colony-forming units (CFUs). At each in-hospital visit, participants take home the appropriate number of MET-2 capsules needed for a 2-week period, packaged in bottles. Loading/booster doses are provided in separate vials from maintenance daily doses. Each vial is stored by the participant at room temperature. MET-2 is meant to be taken after a light meal, preferably in the morning and at the same time every day.

Participants will consume an initial loading dose of 5 g MET-2. An initial MET-2 dose in the range of 10^8^ to 10^12^ CFUs was selected with the aim of ensuring delivery of a sufficient quantity of the MET-2 bacterial community that is expected to colonize the gut. The first loading dose, at baseline, is to be consumed under the supervision of the study staff to ensure immediate safety, and further compliance is assessed using the returned investigational product and by reviewing participants’ personal logs at each in-hospital visit. For the remainder of the 2-week period, the participants will consume 1.5 g of MET-2 per day. The loading dose is repeated for the first 2 days at the week 2 time point, and participants return to the maintenance dose for the remainder of the treatment period. At week 4, participants are assessed for treatment response. Responders remain on the maintenance dose until the end of treatment. Nonresponders are given an additional loading dose (booster dose; Table 1).

**Table 1 table1:** Dosing schedule.

Dose	Baseline to week 2	Weeks 2*-*4	Weeks 4*-*6	Weeks 6*-*8
Loading/booster dose (5 g of MET-2^a^: 10 capsules per day for 2 days)	Days 1 and 2 only	Days 1 and 2 only	Days 1 and 2 (only NR^b^)	N/A^c^
Maintenance dose (1.5 g of MET-2: 3 capsules per day)	Days 3-14	Days 3-14	R^d^: Days 1-14; NR: Days 3-14	Days 1-14

^a^MET-2: microbial ecosystem therapeutic-2.

^b^NR: nonresponders.

^c^N/A: not applicable.

^d^R: responders.

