#### Treatment Success

Treatment success is defined as a reduction in the MADRS/GAD-7 scores by 50% from the baseline. Those who do not meet the 50% threshold are considered nonresponders. Nonresponders at the week 4 visit will be given a booster dose.

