#### Treatment Failure

Treatment failure is defined as same or increased MADRS/GAD-7 scores from pre- to post-treatment.

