### Participants

A total of 10 to 15 eligible participants aged between 18 and 65 years will be recruited from the Kingston area. At the first visit, consent will be obtained from potential trial participants by a study team member and overseen by the principal investigator. Following informed consent, the participants will be screened to ensure that they fit the inclusion criteria (Textbox 1). In this study, we define depression as a confirmed diagnosis of MDD based on the MINI and a score of ≥15 on MADRS; anxiety is defined as a confirmed diagnosis of GAD based on the MINI and a score of ≥8 on the GAD-7. These participants are not to be in a current episode of MDD or GAD and should not have been taking any antidepressant medication. Textboxes 1 and 2 provide the full study criteria. 

Inclusion criteria.Able to provide informed consentNot pregnantWilling to participate in follow-up as part of the studyDiagnosis of major depressive disorder and/or generalized anxiety disorder (GAD) by the mini-international neuropsychiatric interviewCurrent depressive episode with a Montgomery-Asberg depression rating scale score of ≥15 or current GAD episode with a GAD 7-item scale score of ≥8Able to understand and comply with the requirements of the studyAble to provide stool and blood samples

Exclusion criteria.History of chronic diarrheaNeed for regular use of agents that affect gastrointestinal motility (narcotics such as codeine or morphine and agents such as loperamide or metoclopramide)ColostomyElective surgery that will require preoperative antibiotics planned within 6 months of enrollmentPregnant, breastfeeding, or planning to get pregnant in the next 6 monthsAny condition for which, in the opinion of the investigator, the participant should be excluded from the studyCurrent use of any antidepressant/antianxiety drug (eligible to participate after a 4-week washout period)Use of any antibiotic drug in the past 4 weeks (may be eligible to participate after a 4-week washout period)History of alcohol or substance dependence in the past 6 monthsDaily use of probiotic products in the past 2 weeks (may be eligible to participate after a 2-week washout period)Use of any type of laxative in the last 2 weeksConsumption of products fortified in probiotics

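### The responder rule counts a 50% fall on either MADRS or GAD-7, including a scale that was never elevated at entry, and the same rule decides who gets the week 4 booster

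*Protocol article*

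**What the plan says.** All places are in the protocol article.

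- **Primary Objective:** "Those with a 50% reduction in the GAD-7 and/or MADRS scores will be considered successful responders to treatment".
- **Treatment Success:** "Treatment success is defined as a reduction in the MADRS/GAD-7 scores by 50% from the baseline". The slash is not explained there, but the Primary Objective and Statistical Analyses sections both settle it as either scale.
- **Statistical Analyses:** "Those who have an improvement of at least 50% in MADRS or GAD-7 scores will be considered responders".
- **Entry (Participants, inclusion criteria):** the two severity thresholds are alternatives: "score of ≥15 or current GAD episode with a GAD 7-item scale", the latter at 8 or more. One elevated scale is enough.
- **Dosing (Study Design and Treatment Success):** response is assessed at week 4. "Responders remain on the maintenance dose until the end of treatment", whereas "Nonresponders at the week 4 visit will be given a booster dose". No separate week 4 criterion is given, so the either-scale rule is the only one available for this decision.
- **Outcome Measures and Table 2:** both scales are scored in every participant from screening to week 10, and change on each is the primary outcome measure.

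No section links response to the scale on which the participant qualified, sets a minimum baseline for the scale that is counted, or says what happens if the other scale worsens.

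**The concern.** In a sample that may have depression, anxiety or both, accepting improvement on either scale is understandable. The difficulty is that the scale counted need not be one that was elevated. A proportional criterion is easy to meet from a low starting score, where a change of one or two points is half of the total. A person admitted for depression can therefore be called a successful responder because of a small movement in a GAD-7 score that was below threshold from the start, while the depression score stays put or rises.

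Two things depend on the label. It is the success criterion in the primary objective, so it is likely to be the figure readers take away. It also sets the dose at week 4: the person just described is not given the extra loading dose that the plan provides for people who have not responded.

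**Working it through.** The article states no expected response rate and no power calculation, so there is no figure of its own to reproduce. The check is of logic and of dose.

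**1. A worked case under the rule as written.** Illustrative scores: MADRS 24 rising to 27, GAD-7 4 falling to 2.

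- Entry: MADRS 24 ≥ 15, so eligible; GAD-7 4 < 8, so not elevated.
- MADRS change: (24 − 27)/24 = −12.5%, a worsening.
- GAD-7 change: (4 − 2)/4 = 50%, which meets the criterion.
- Either scale suffices, so the participant is a responder and, if this is week 4, gets no booster.

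**2. Points needed for a 50% fall.** With whole-number scores and baseline b, the smallest sufficient fall is b/2 rounded up.

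| Baseline | Smallest sufficient fall |
|---|---|
| GAD-7 of 1, 2, 3, 4, 5, 6, 7 (below threshold) | 1, 1, 2, 2, 3, 3, 4 |
| GAD-7 of 8 (threshold) | 4 |
| MADRS of 1 to 14 (below threshold) | 1 to 7 |
| MADRS of 15 (threshold) | 8 |

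A participant admitted on MADRS alone can thus become a responder through a GAD-7 fall of 1 to 4 points, against 8 points on MADRS at its entry minimum. The thresholds apply at screening. If baseline means the week 0 score and MADRS has drifted below 15 by then, the 8 would be lower.

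**3. Dose consequence.** Inputs from Study Design and Table 1: 0.5 g per capsule; loading or booster 10 capsules a day for 2 days; maintenance 3 capsules a day.

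| Period | Week 4 responder | Week 4 nonresponder |
|---|---|---|
| Weeks 0–2 | 2×10 + 12×3 = 56 capsules = 28 g | 28 g |
| Weeks 2–4 | 28 g | 28 g |
| Weeks 4–6 | 14×3 = 42 capsules = 21 g | 2×10 + 12×3 = 56 capsules = 28 g |
| Weeks 6–8 | 42 capsules = 21 g | 21 g |
| Total | 98 g | 105 g |

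The difference is 7 g: 7/28 = 25% of that fortnight's dose, but 7/105 = 6.7% of the whole course.

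**4. Weight of one case.** The Results section reports 12 participants with at least one post-baseline visit. One reclassified participant moves the rate by 1/12 = 8.3 percentage points.

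**5. Precision of per-scale rates.** Each per-scale denominator is at most 12. The two sum to at least 12, because everyone met at least one threshold. Exact (Clopper-Pearson) 95% intervals at an observed 50%, where the denominators 8 and 6 are assumptions:

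- 6/12: 21% to 79%
- 4/8: 16% to 84%
- 3/6: 12% to 88%

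**The case against.** The strongest reply is that this is a design preference. The sample is mixed, both scales are primary outcome measures in everyone, and the sections that spell out the success rule agree. That stands as far as it goes: success is neither ambiguous nor self-contradictory. It does not answer the point that the scale counted may never have been elevated.

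A second reply is that the Statistical Analyses section says success and failure are assessed individually, which might mean scale by scale, each for its own condition. The more natural sense is participant by participant. Even on the other sense, the next sentence joins the two scales with an or into one responder label.

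A third reply is that little hangs on it: the repeated measures ANOVA and paired *t* tests are on scores, and no test of the responder rate is stated. This stands, and a reader who inferred that the planned tests are invalid would go too far. Those scores are not wholly untouched, however, because the label decides who receives a booster before week 6.

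A reader might also infer an inflated response rate of a particular size. The article gives neither a response probability per scale nor a correlation between the scales, so no such figure can be derived. Opposite movement on the two scales may be uncommon, since the Introduction describes GAD as a common comorbidity of MDD. Quoting the 25% dose gap alone would likewise overstate matters, given 6.7% over the course.

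Finally, a reader might conclude that one participant can be both a success and a failure, from "Treatment failure is defined as same or increased MADRS/GAD-7 scores from pre- to post-treatment". That follows only if the slash there means either scale; if it means both, there is no overlap. No test or dose uses the failure label, and a condensed article may leave such detail to the full protocol. It is a wording note only.

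**Conclusion.** The point holds in limited form. Applied exactly as written, the responder rule can call a participant successful when the qualifying scale did not improve or worsened, and can withhold the week 4 booster from that person. This follows from the text alone; the calculations assume only whole-number scores and the doses in Table 1.

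The size per case is 8.3 percentage points on a denominator of 12, and 7 g of MET-2. The number of cases is unknown and may be zero. The point bears on how the responder count is read and, through the booster, possibly on scores from week 6 on. It does not overturn the score-based analyses. It is worth acting on because the remedy is cheap and the label belongs to the primary objective.

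**What to change.** Recruitment is complete and analysis is under way, so the published definition should be kept and supplemented, not replaced:

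1. Report the either-scale responder count as published.
2. Beside it, labelled post hoc, report the proportion with a fall of at least 50% on MADRS among participants who entered with MADRS ≥ 15, and on GAD-7 among those who entered with GAD-7 ≥ 8, each with its denominator and an exact interval.
3. Show the MADRS-by-GAD-7 cross-table of outcomes, so that any participant who improved on one scale and worsened on the other is visible.
4. Base any efficacy statement about responders on the per-scale figures.
5. State in a few words whether the slash in the failure definition means either scale or both.

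No new assessment is needed, as both scales are already collected at every visit. The costs are the smaller denominators and wide intervals shown above, and possibly a lower headline count than the either-scale figure. Week 4 dosing cannot be changed; the report can say how many participants were denied a booster on the strength of a sub-threshold scale.

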### Outcome Measures

#### Clinical Measures

Mood, anxiety, and GI symptoms and sleep quality will be assessed at all treatment visits. At week 10, only the MADRS and GAD-7 will be administered. The primary outcome measure will be mood and anxiety symptoms measured biweekly by changes in the MADRS and GAD-7 scores, respectively. The clinical measures include self-rated and clinician-rated measures. The self-rated questionnaires that will be used are the GAD-7 to assess anxiety symptoms and severity, the Snaith-Hamilton pleasure scale to assess anhedonia, quick inventory of depressive symptomatology to assess depressive symptoms, the gastrointestinal symptom rating Scale (GSRS) to assess GI symptoms, the Toronto side effects scale (TSES) to assess tolerability of the therapeutic product, and the Pittsburgh sleep quality index to assess subjective sleep quality. The clinician-rated questionnaires and interviews are the MADRS to assess depressive symptoms and severity, the clinical global impressions scale to assess illness severity and improvement, and the childhood experience of care and abuse questionnaire to assess early life stress and environmental risk factors associated with upbringing. Table 2 gives more details on the scales used in assessing outcome measures.

**Table 2 table2:** Study visit schedule.

Procedure		Screening	Week 0	Week 2	Week 4	Week 6	Week 8	Week 10

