#### Safety and Tolerability

Participants will use a personal mood and symptom log to track any symptoms that they have been newly experiencing since the beginning of treatment, assess the tolerability of treatment, and keep track of their mood and sleep. AEs will be assessed and recorded at all in-hospital visits and on phone calls; they will be categorized by frequency, severity, and causality. The frequencies and severity of AEs will be collected on a questionnaire from the first day of the assigned study treatment through 14 days following the last assigned study treatment. Investigational product safety will be assessed via recorded symptoms and AEs. Investigational product tolerability will also be assessed using the TSES and GSRS during all visits except screening.

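### Ten per-visit tests on two primary scales with no named primary contrast (roughly 25–35% chance of a false positive); separately, the analysis runs to week 10 for six scales that stop at week 8

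*Protocol article*

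**What the plan says.** The Clinical Measures section defines the primary outcome: "The primary outcome measure will be mood and anxiety symptoms measured biweekly by changes in the MADRS and GAD-7 scores, respectively". In Table 2 both scales are marked at week 0 and at weeks 2, 4, 6, 8 and 10.

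The Statistical Analyses section gives two procedures for the clinical measures. The first is an overall model: "Repeated measures analysis of variance (ANOVA) will be used to analyze changes in clinical measures from baseline to week 10". The second is a set of per-visit comparisons: paired t "tests will be used to compare clinical measure means at each time point with the baseline". The section names no primary visit or contrast and does not make the t tests depend on the ANOVA. For missing values it says: "In the event of missing data, the data from the last time point will be projected forward".

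On the visit schedule, the Clinical Measures section says: "At week 10, only the MADRS and GAD-7 will be administered". Table 2 agrees: CGI, Snaith-Hamilton, QIDS, PSQI, TSES and GSRS are marked from week 0 to week 8 and not at week 10. The Safety and Tolerability section says something different for two of them: "Investigational product tolerability will also be assessed using the TSES and GSRS during all visits except screening".

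**The concern.** There are two separate problems.

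First, followed as written, the plan gives ten opportunities to report improvement on a primary scale and does not say which one answers the primary objective. A significant result at any visit on either scale could be presented as the finding. Other parts of the article do not settle the end point. Treatment Failure compares scores before and after treatment, Treatment Success names no final visit, and the Results section expects improvement up to week 10, two weeks after dosing ends. Symptom change is the primary objective and safety is secondary, so the choice bears on the trial's main conclusion.

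Second, the analysis range does not match the schedule. The statement that the ANOVA "will be used to analyze changes in clinical measures from baseline to week 10" covers clinical measures in general, but six of the eight repeatedly administered scales have no week 10 assessment. For TSES and GSRS, the tolerability scales, the text and Table 2 disagree on whether week 10 is assessed at all.

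**Working it through.** The article states no significance level, power or familywise error rate, so there is no figure of its own to reproduce.

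**Inputs from the article**
- Primary scales: 2 (Clinical Measures).
- Post-baseline visits for each: 5 (Table 2).
- Test: paired t against baseline at each visit (Statistical Analyses).
- Sample size: 10 to 15 planned (Participants); 21 enrolled and 12 completed (Results).

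**Assumed, because not stated**
- Two-sided 0.05 per test.
- Correlation between visits 0.3–0.9, either equal for all pairs (compound symmetry) or decaying with time (AR(1)).
- Correlation between scales 0–0.7.

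**Step 1: number of primary tests.** 2 × 5 = 10.

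**Step 2: reference value under independence.** 1 − 0.95^10 = 1 − 0.599 = 0.401, or 40%.

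**Step 3: allow for dependence.** All five contrasts on a scale share one baseline and come from the same people. With equal variances and compound symmetry at correlation r, two changes from baseline have covariance σ²(1 − r) and variance 2σ²(1 − r). Their correlation is therefore 0.5 whatever r is. Under AR(1) neighbouring visits are more alike and the familywise rate is lower. Null trials were simulated from a multivariate normal distribution with n = 10, 12, 15 and 21 and 12,000–40,000 replicates per setting. Compound symmetry gave 29–35%, AR(1) 24–33%, and the two together 24–35%.

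**Step 4: two variants.** One carries the last value forward, with 9 of 21 participants (21 − 12 = 9) assumed to stop at a random visit after week 0. The other counts a t test only if that scale's repeated measures F test, without a sphericity correction, is significant at 0.05.

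| Visit structure | Visit corr. | Scale corr. | n = 12, as written | n = 21, carry-forward | n = 12, gated by ANOVA |
|---|---|---|---|---|---|
| Compound symmetry | 0.5 | 0.5 | 32.5% | 29.4% | 7.1% |
| Compound symmetry | 0.7 | 0.5 | 32.1% | 28.3% | 6.9% |
| Compound symmetry | 0.7 | 0.7 | 30.4% | 26.7% | 6.5% |
| AR(1) | 0.5 | 0.5 | 30.1% | 26.8% | 9.5% |
| AR(1) | 0.7 | 0.5 | 28.7% | 25.6% | 11.1% |
| AR(1) | 0.7 | 0.7 | 26.6% | 24.1% | 10.1% |

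**Step 5: after the fix.** One visit on both scales, uncorrected, gives at most 1 − 0.95² = 9.75% (the independent case). Holm across the two scales (0.025 for the smaller p value, then 0.05 for the larger) holds this at 5% or less.

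**Step 6: schedule against analysis range.**

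| Scales | Last visit in Table 2 | ANOVA range in Statistical Analyses |
|---|---|---|
| MADRS, GAD-7 | Week 10 | Week 10 (agrees) |
| CGI, Snaith-Hamilton, QIDS, PSQI | Week 8 | Week 10 (no data) |
| TSES, GSRS | Week 8 in Table 2; every visit after screening in Safety and Tolerability | Week 10 (no data under Table 2) |

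The mismatch involves none of the ten primary tests, so it adds nothing to the rates above.

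**The case against.** The best defence is that much of this is silence in a condensed article. A correction, a significance level or a testing order may be in the statistical analysis plan, which is not shown, and their absence alone is not a defect. The ANOVA is listed before the t tests, and if it is meant as a gate the rate drops to about 7–11%. The text leans towards week 10 in several places, and including an off-treatment visit is deliberate, since the primary objective covers the period after treatment. This is also a small, open-label phase 1 trial that acknowledges its size and the lack of a placebo arm. No multiplicity correction replaces a control group.

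Most of this is fair, and it limits the point. What stands is what the article does fix: two unranked primary scales, biweekly measurement as the primary outcome, and a test at every visit, with no gate stated.

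Three stronger readings are tempting and are not supported.
- That the false-positive rate is certain to exceed 30%. That figure lies inside the plausible range and is not a floor: AR(1) correlation or carry-forward can bring the rate to about 24%.
- That the week 10 mismatch drives the inflation. Both primary scales are measured at week 10.
- That week 10 results for six scales would be manufactured. This needs the carry-forward rule to apply to assessments that were never scheduled. The rule concerns missing data, and the article says plainly which two scales are given at week 10.

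**Conclusion.** The concern holds as two separate points of modest weight.

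On multiplicity, the plan as written gives ten primary tests and no named primary contrast. The chance of at least one false positive is roughly 25–35%, five to seven times the nominal 5%. This rests on an assumed two-sided 0.05 per test, no true change on either scale, and the stated correlation ranges. It does not apply if the unseen analysis plan names a contrast, corrects the tests or gates them on the ANOVA.

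On consistency, the ANOVA range conflicts with the visit schedule for six scales, and the tolerability text conflicts with Table 2 for TSES and GSRS. These conflicts are in the document itself and need no assumption. Their effect is ambiguity about what is analysed at week 10, not a higher error rate for the primary scales.

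**What to change.** - Name one primary contrast per scale, for example change from week 0 to week 8 (end of treatment) on MADRS and on GAD-7, with Holm across the two.
- Report the other visits as estimates with 95% confidence intervals and no significance claims.
- Report week 10 as a separate off-treatment durability contrast, for example week 8 to week 10.
- Date this choice. The article says recruitment is complete and analysis is under way, so label the choice post hoc if results have already been seen.
- Limit the analysis of CGI, Snaith-Hamilton, QIDS, PSQI, TSES and GSRS to weeks 0–8, and state that carry-forward does not apply to assessments that were not scheduled.
- Reconcile the Safety and Tolerability sentence on TSES and GSRS with Table 2.

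No new data are needed, only wording and a dated record of the decision. The cost is that early-visit p values can no longer be claimed as confirmation. If results have been seen, the named contrast also loses the standing of a prespecified one.

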**Objective:**

The primary objective of this study is to assess subjective changes in mood and anxiety symptoms before, during, and after administration of MET-2. The secondary objectives of this study are to assess the changes in metabolic functioning and the level of repopulation of healthy gut bacteria, the safety and tolerability of MET-2, and the effects of early stress on biomarkers of depression/anxiety and the response to treatment.

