**Methods:**

Adults experiencing depressive or anxiety symptoms will be recruited from the Kingston area. These participants will orally consume an encapsulated MET-2 once daily—containing 40 strains of purified and laboratory-grown bacteria from a single healthy donor—for 8 weeks, followed by a 2-week treatment-free follow-up period. Participants will undergo a series of clinical assessments measuring mood, anxiety, and GI symptoms using validated clinical scales and questionnaires. Molecular data will be collected from blood and fecal samples to assess metabolic changes, neurotransmitter levels, inflammatory markers, and the level of engraftment of the fecal samples that may predict outcomes in depression or anxiety.

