**Results:**

Given the association between the gut bacteria and the risk factors of depression, we expect to observe an improvement in the severity of depressive and anxiety symptoms following treatment, and we expect that this improvement is mediated by the recolonization of the GI tract with healthy bacteria. The recruitment for this study has been completed, and the data obtained are currently being analyzed.

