#### Secondary Objectives

The secondary objectives are to assess changes in metabolic functioning/levels before, during, and after treatment; to assess safety and tolerability, including adverse events (AEs) with a severity of grade 2 or above; and to assess potential correlation between early life stress (childhood emotional/physical/sexual abuse history, etc) and changes in MDD biomarkers as well as response to treatment.

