## Results

The study received approval from the Queen’s University Health Sciences and Affiliated Teaching Hospital Research Ethics Board on March 28, 2019. Participant recruitment began in May 2019. As of March 2020, we have enrolled 21 participants, of which 12 participants completed the study with at least one visit postbaseline. We have completed recruitment for this study and are currently in the process of analyzing data. We expect to see improvement in depressive and anxiety symptom scores from baseline to week 10, to be mediated by a decrease in pro-inflammatory markers and an increase in anti-inflammatory markers. Furthermore, we hope to see lasting changes in the microbiome composition reflecting a similar composition to that of the donor by the end of the study.

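### The statistics paragraph analyses stool only as a diversity score, which does not identify taxa, so the stated analysis does not answer the repopulation question that the planned 16S data could address

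*Protocol article*

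**What the plan says.** Several parts of the protocol article ask which bacteria are present after treatment:

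- Abstract, Objective: a secondary objective is to "assess the changes in metabolic functioning and the level of repopulation of healthy gut bacteria".
- Abstract, Methods: the molecular data are to assess "the level of engraftment of the fecal samples that may predict outcomes in depression or anxiety".
- Abstract, Results: "we expect that this improvement is mediated by the recolonization of the GI tract with healthy bacteria".
- Results (main text): the authors hope for "lasting changes in the microbiome composition reflecting a similar composition to that of the donor by the end of the study".

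Molecular Analysis plans 16S sequencing of stool to describe composition before, during and after treatment. Table 2 schedules stool at weeks 0, 2, 4, 8 and 10.

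Statistical Analyses then gives stool two sentences. In the first, "stool samples will be analyzed to provide diversity scores, which will then be compared using paired" t tests and repeated measures ANOVA. The second reads: "Changes in diversity scores will be compared with clinical scores to assess for correlations". It states no measure of engraftment, no product or donor reference and no mediation analysis.

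The main-text Secondary Objectives begin "The secondary objectives are to assess changes in metabolic functioning/levels before, during, and after treatment" and go on to safety, tolerability and early life stress. Repopulation appears in the abstract's list but not in this one.

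**The concern.** Repopulation, engraftment and resemblance to the donor are all questions about the identity of taxa. A within-sample diversity index summarises how many taxa there are and how evenly they are spread, whatever they are. If the paragraph is followed as written, the trial could report an unchanged microbiome when the product strains have engrafted, or an improved one when none has. A correlation between diversity change and symptom change could then be read as support for the recolonization mechanism, which it does not test. The primary symptom outcomes are not affected. What is at stake is one secondary objective and the mechanistic conclusion.

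**Working it through.** The plan states no figure for this endpoint, so there is none to reproduce. The check is whether a diversity score can stand in for repopulation.

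**Inputs from the document.** The product has 40 defined strains (Introduction, Microbial Ecosystem Therapeutics). The planned sample is 10 to 15 (Participants). 12 participants completed with at least one post-baseline visit (Results).

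**Assumptions.** The abundance vectors are invented to test the logic and do not predict this trial's data. Two-sided alpha 0.05 and 80% power are also assumed, because the document states neither.

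**Step 1: the simplest case.** Shannon diversity is H = −Σ p ln p. For 40 equally abundant taxa, H = −40 × (1/40) × ln(1/40) = ln 40 = 3.69. This holds whether the 40 taxa are the MET-2 strains or 40 others. The paired difference between two such guts is 0, although they share no taxon.

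**Step 2: uneven communities.** The baseline is 100 non-product taxa with lognormal abundances. The reference profile is the 40 product strains at 1/40 each. Simpson is 1 − Σ p². Bray-Curtis distance on relative abundances is 1 − Σ min(a, b).

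| State | Shannon | Simpson | Taxa | Product strains | Product share | Bray-Curtis to reference |
|---|---|---|---|---|---|---|
| Baseline | 4.286 | 0.981 | 100 | 0/40 | 0 | 1.00 |
| All 40 strains replace the 40 most abundant residents at the same abundances | 4.286 | 0.981 | 100 | 40/40 | 0.70 | 0.38 |
| The same 40 residents replaced by non-product taxa | 4.286 | 0.981 | 100 | 0/40 | 0 | 1.00 |
| Residents become even, nothing engrafts | 4.605 | 0.990 | 100 | 0/40 | 0 | 1.00 |

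The first three rows agree on all three diversity measures because H, Simpson and richness depend only on the set of abundances and do not change when taxa are relabelled. The last row is ln 100 = 4.605 and 1 − 1/100 = 0.990. A rise in diversity is thus neither necessary nor sufficient for engraftment. The product-referenced columns separate full engraftment from the other states.

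**Step 3: precision of the planned correlation.** The critical value is r = t/√(n − 2 + t²). At n = 12, t(10) = 2.228, so r = 2.228/√(10 + 4.964) = 0.576. The true r needed for 80% power is tanh[(1.960 + 0.842)/√(n − 3)].

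| n | r needed for p < 0.05 | True r for 80% power |
|---|---|---|
| 10 | 0.63 | 0.79 |
| 12 | 0.58 | 0.73 |
| 15 | 0.51 | 0.67 |

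An observed r of 0.5 at n = 12 has a 95% CI of tanh(0.549 ± 1.96/3), about −0.10 to 0.83. Using n = 12 assumes 12 usable stool pairs, which the document does not confirm. These limits apply to any correlation at this size, including one with a better stool measure. They support an exploratory label and are not a reason to prefer one measure over another.

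**The case against.** The strongest reply is that a journal article condenses the full plan. It names engraftment as something to be assessed and plans sequencing for composition, so the choice of index, reference and engraftment definition may sit in a document not shown. Naming one measure does not exclude others. This part stands: a reader might infer that the trial cannot answer the repopulation question, and the document does not support that, because the 16S data would allow an answer. It does not dispose of the point. Statistical Analyses does more than stay silent: it names the stool variable, both tests and the link to symptoms, and that variable does not match the question.

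Second, no index is named, and a distance from baseline or donor is also one number per sample. That is fair, so the within-sample reading is an inference. It is the likelier one: the Gut Brain Axis section treats lower diversity as a property of a depressed patient's own microbiota, and a score compared with baseline by paired t test fits that use. If a donor distance was meant, the text needs to say so. The same section gives diversity a rationale as a partial outcome, which is a reason to keep it as descriptive.

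Third, mediation is only an expectation. A reader might infer that the trial plans to claim mediation from a correlation. The statistics paragraph promises only correlations, and the Discussion already concedes the small sample and the missing placebo arm. What remains is a matter of wording. The abstract names recolonization as the mediator and the main Results section names inflammatory markers, and no mediation analysis is stated for either.

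**Conclusion.** The point holds as a mismatch between the stated question and the stated analysis. Under the within-sample reading, the only stool variable analysed and correlated with symptoms can be unchanged under full engraftment (Shannon 4.286 to 4.286, 0/40 to 40/40 strains) or rise with none (4.286 to 4.605, 0/40 throughout). These examples show what the score can miss. They do not estimate how often that would happen here. The conclusion rests on the within-sample reading and on taking the abstract's objective as binding despite its absence from the main-text list. The question is unanswered by the stated analysis but is not unanswerable. This merits correction for a secondary objective and leaves the primary outcomes untouched.

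**What to change.** In Statistical Analyses, add two measures from the 16S data already planned:

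- (a) At each stool visit, the change from week 0 in the relative abundance and number of taxa matching the 40-strain MET-2 mixture. Increases count as well as new appearances, because a strain may belong to a 16S taxon that was already present.
- (b) A beta-diversity distance, such as Bray-Curtis, to the MET-2 product profile. Use donor stool as the reference only if it has been sequenced, since the article describes no such sequencing.

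Take the week 0 to week 8 change as the repopulation measure and week 10 for persistence. State that 16S has limited power to identify strains. Recruitment is closed and analysis is under way, so label the measures exploratory and date them as added after recruitment closed. Report their correlations with MADRS and GAD-7 change with confidence intervals. Keep diversity as descriptive.

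In the Abstract's Results and the main Results section, replace *mediated by* with *associated with*. Reconcile the two lists of secondary objectives so that repopulation appears in both or in neither.

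The cost is modest extra bioinformatic work and a reference 16S profile of the product. No new participants, visits or stool samples are needed.
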